**Figure 1 figure1:**
[figure not shown]
Timeline for Communities Organizing for Power through Empathy (COPE) stepped-wedge cluster randomized trial design and assessment. C1-3: COPE sessions 1-3; H1-2: house meetings 1-2; T1: baseline measurement period; T2-5: time points 2-5. *Steps 4 and 5 follow the same sequence as steps 1-3.

## Methods

### Overview and Study Design

This study uses a pragmatic mixed methods approach to examining the effectiveness and practical relevance of COPE in a real-world context [75]. We will collect and examine qualitative data to address aim 1, capturing contextual information about cluster-level and individual-level factors that influence the feasibility, implementation, and acceptability of COPE. We will approach aim 2, the test of intervention effectiveness, using a SW-CRT with a rolling enrollment design. As a pragmatic 2-arm SW-CRT, the study has two conditions or arms: (1) the intervention arm, in which clusters of participants begin by engaging in the COPE intervention, and (2) the attention control arm, in which clusters of participants begin by attending “house meetings” (listening sessions) before switching to the COPE intervention. A cluster is defined as a single CBO (or in a rare case, a pair of related CBOs). Clusters are eligible to participate if they are CBO members of TBR. Steps are clusters grouped by availability (ie, feasible start date as provided by CBO leadership). At the initiation of a step and before participant enrollment, clusters are randomized into study arms.

As a SW-CRT, every cluster will provide before and after observations, and will switch from control to intervention, but not at the same point in time (Figure 1) [74]. At study outset, clusters are assigned by the first author to 1 of 5 sequential steps: 2 in step 1, 4 in steps 2 and 3, and 6 in steps 4 and 5 (Figure 1). At the initiation of a step, clusters will be randomized by the first author into the intervention and control arms using a random number generator. Allocation into intervention or control arms will not be concealed at either the cluster or individual level, nor will clusters or participants be blinded, as doing so is not feasible given the group-based nature of the intervention and community-based nature of the study implementation. We will include controls to account for temporal and enrollment differences. Presurvey data collection will occur immediately before the start of the intervention within each cluster. After the third data collection time point, the clusters in the attention control arm will switch to receive the COPE intervention (see Figure 1 for the design timeline).

To accomplish aim 1, we are using the Consolidated Framework for Implementation Research [76] to examine factors that affect intervention implementation and program efficacy, as well as standardized measures of perceptions of feasibility, acceptability, and cultural appropriateness. We will conduct quantitative assessments, interviews, and focus groups with community facilitators (CFs), institutional leaders, and participants (see Multimedia Appendix 1 for facilitator interview guide). In addition, to align with our CBPR approach, our research team includes a group of community members we refer to as the “CBPR strategy team” who guided the adaptation process that developed COPE and will guide the study design, implementation, and analysis of findings. For example, we presented them with options for measures of mental health and discussed the overall survey design. The team chose measures and approved the final survey instrument. We also worked with the team to discuss options for implementation of the COPE sessions and recruitment. As we analyze data, we will review findings and papers developed with the team, along with other community members. In our analyses for aim 1, we will integrate the methods by combining themes from interviews and focus groups with analyses of implementation measures.

To accomplish aim 2, we are collecting cohort data from participants in clusters in both arms assessed along measures of mental health, coping, social support, and community resilience at 5 time points (see Figure 1 for study design and data collection time points). Participants will complete assessments at each time point before content delivery using Qualtrics survey software loaded on a tablet. In cases where participants are unable to use a tablet (eg, discomfort with technology or visual impairment), they will complete the assessment on paper and research staff will enter the data into the software. Participants will be given a US $10 gift card at the completion of each questionnaire.

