**Methods:**

The Consolidated Framework for Implementation Research guides our analysis of data collected from surveys, fidelity and field notes, interviews, and focus groups to examine aim 1. We examine aim 2 primarily via a 2-arm pragmatic stepped-wedge cluster randomized trial (SW-CRT) with individuals (approximately n=300) in clusters (faith-based and secular community-based organizations; approximately n=15) in a disaster-prone community in the US Gulf Coast. The cluster-based design implemented in steps supports the community-based nature of the study where timelines differ by organization. A total of 5 self-assessments will be conducted both in person and via email at later time points. We will integrate mixed methods in our analyses for aim 1 by combining themes from interviews and focus groups with implementation measures, and for aim 2 by constructing a data matrix to combine findings from the SW-CRT with thematic analyses of field notes and interviews.

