### Sampling Strategies and Sample Size

Multilevel mixed methods, with convenience, purposive, and probability sampling techniques at different levels of analysis, in this case clusters and individuals, will be used as different strategies are required for each aim. Convenience sampling will be applied in the initial phases of the study during the adaptation process to pilot-test the COPE intervention’s components with accessible participants from across the clusters to ensure broad acceptability and commitment to participation in the SW-CRT. For aim 1, maximum variation sampling will be used to gain perspectives from a heterogenous pool of participants and facilitators [80]. This will include purposive sampling of participants from different institutions to gain a diverse set of perspectives on barriers or facilitators that impact implementation of COPE.

For the SW-CRT component of aim 2, we did a power analysis to estimate the required sample size for a target power of 80%. We assumed a standardized moderate effect size of 0.3, 5 time points, a conservative intraclass correlation coefficient (ICC) of 10% (10% site-level and 90% person-level variation), and a within-person correlation of 0.3. The power analysis results indicated that 300 participants at 15 sites with 20 participants per site achieves the target power. We also did sensitivity analyses varying the effect size, ICC, within-person correlation, and number of sites, and with very conservative estimates the target power can be achieved.

After clusters are randomized into groups, participants will be recruited by CFs and project staff using convenience sampling techniques. As one cluster includes a large Spanish-speaking population among its membership, COPE will be delivered to participants in that cluster in Spanish by native Spanish-speaking bilingual facilitators and participants will be provided materials in Spanish.

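### The clusters assigned to the five steps add up to 22 or 12, not to the 15 sites of 20 on which the sample size rests

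*Protocol article*

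**What the plan says.** Three places in the protocol article fix the number of clusters.

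- **Overview and Study Design:** "clusters are assigned by the first author to 1 of 5 sequential steps", and the counts are "2 in step 1, 4 in steps 2 and 3, and 6 in steps 4 and 5". Figure 1 is cited for this and is not shown in the text available. The same section defines a cluster as one community organization or, rarely, a related pair.
- **Sampling Strategies and Sample Size:** the aim was to "estimate the required sample size for a target power of 80"%, assuming a "standardized moderate effect size of 0.3, 5 time points", an intraclass correlation of 10% and a within-person correlation of 0.3. The conclusion is that "300 participants at 15 sites with 20 participants per site achieves the target power". Sensitivity analyses that varied the number of sites, among other inputs, are reported without figures.
- **Abstract, Methods:** "individuals (approximately n=300") in clusters ("faith-based and secular community-based organizations; approximately n=15").

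**The concern.** The design section and the sample size section describe the same set of clusters, so the step counts should sum to the number of sites in the power statement. They do not. Randomization is by cluster within step, so the cluster count fixes the information available between arms and the degrees of freedom behind each confidence interval. It also sets either the total sample or the cluster size, depending on which is held fixed. If the article stays as it is, a reader of the results cannot tell whether a final count of 12, 15 or 22 clusters is the plan, a shortfall or an expansion.

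**Working it through.** **1. The plan's own product.** 15 sites × 20 participants = 300. This reproduces exactly and agrees with the abstract.

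**2. Sum of the step counts.** The sentence does not say whether 4 and 6 apply to each step or to the pair.

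| Steps 2 and 3 | Steps 4 and 5 | Sum | Against 15 |
|---|---|---|---|
| 4 each | 6 each | 2+4+4+6+6 = 22 | +47% |
| 4 together | 6 together | 2+4+6 = 12 | −20% |
| 4 each | 6 together | 2+4+4+6 = 16 | +7% |
| 4 together | 6 each | 2+4+6+6 = 18 | +20% |

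The first two rows read both halves of the sentence in the same way; the last two do not. The rare paired organizations do not close the gap, because a pair still counts as one cluster.

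**3. What this implies for size.** At 20 per cluster: 22 × 20 = 440 and 12 × 20 = 240. At 300 participants: 300/22 = 13.6 and 300/12 = 25 per cluster.

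**4. What this implies for power.**

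*Inputs from the sample size section:* effect 0.3 SD, five time points, intraclass correlation 0.10, within-person correlation 0.3.

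*Inputs from the design section:* COPE-first clusters have exposure 0,1,1,1,1. House-meeting clusters have 0,0,0,1,1, because they switch after the third assessment.

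*Assumptions, since the article gives no alpha or power formula:* two-sided 5%; arms split as evenly as possible; fixed time effects; a cluster effect that is constant over time; total variance 1, made up of cluster 0.10, participant 0.20 (0.30 − 0.10) and residual 0.70.

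For *k* clusters of size *m*, the vector of a cluster's period means has variance V = 0.10 J + (0.20 J + 0.70 I)/m, where J is the all-ones matrix. The variance of the effect estimate is the leading element of (Σ D′V⁻¹D)⁻¹, where D holds the exposure column and the time indicators. Normal power is Φ(0.3/SE − 1.96). The t version uses the noncentral t with k − 2 degrees of freedom and noncentrality 0.3/SE. For 15 × 20 and five time points, SE = 0.0867, so 0.3/0.0867 = 3.46 and Φ(3.46 − 1.96) = 93%.

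| Clusters × size | N | Five points, normal / t | T1–T3 only, normal / t |
|---|---|---|---|
| 12 × 20 | 240 | 87% / 80% | 70% / 61% |
| 15 × 20 | 300 | 93% / 89% | 79% / 72% |
| 22 × 20 | 440 | 99% / 98% | 92% / 89% |
| 12 × 25 | 300 | 93% / 88% | 78% / 69% |
| 22 × 13.6 | 300 | 94% / 91% | 81% / 77% |

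If the correlation of 0.3 is taken as holding within cluster instead, normal power rises slightly. At 12 × 20 it becomes 90% over five points and 73% over T1–T3; at 15 × 20 it becomes 95% and 82%.

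**The case against.** Much can be said for the plan.

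- **Figure 1 may show the clusters per step.** It may, and so it would be too strong to say that the number to be randomized is undefined. But if it shows the allocation in the sentence, it can only select one of the four totals, and none is 15.
- **The abstract qualifies both figures as approximate.** That covers 16, which is one of the mixed readings. That reading takes 4 as per step and 6 as per pair within one sentence, which is strained. The qualifier does not stretch to 12 or 22, and the sample size section gives 15 × 20 without it.
- **The power statement gives a sufficient size, not a cap.** It is fair that planning 22 clusters when 15 suffice would not invalidate the calculation. The article does not say this was the intention, however, and 22 clusters of 20 would be 440 participants against the abstract's 300 or so.
- **Power is hardly affected.** This objection largely stands. With 300 participants held fixed, five-point power under the normal approximation is the same to within a percentage point for 12, 15 or 22 clusters.

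A reader might infer that the trial is underpowered, or that the quoted power belongs to some other trial. The article supports neither. Its stated basis is five time points, on which even 12 × 20 reaches about 80% in the less favorable t version. The clear shortfall at 12 × 20 is confined to the T1–T3 contrast, which is not named as the basis for power.

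A reader might also argue from arm-splitting that each step needs an even count. The article states no 1:1 ratio, and six clusters shared equally over steps 4 and 5 would be three each.

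**Conclusion.** The contradiction is real and needs nothing beyond addition: the step counts give 22 or 12 on a consistent reading, 16 or 18 on a mixed one, and never the 15 in the sample size section. The effect on planned size is 440 or 240 participants at 20 per cluster, or cluster sizes of about 13.6 or 25 at 300. It is more than a slip of wording, because cluster count and total sample are figures on which the trial relies. It does not show inadequate power. The power figures rest on the assumed alpha, on a cluster effect that does not vary over time, and on k − 2 degrees of freedom for the t version, so they illustrate the scale and do not replace the plan's calculation.

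**What to change.** State the number of clusters in each step, making plain whether each count is per step or per pair, and give one total. Align the abstract, Overview and Study Design, and Sampling Strategies and Sample Size on that total, the expected cluster size and the overall number of participants. Restate power at those values. If 15 was a minimum and more clusters were planned as a margin, say so. This takes a text correction and one recalculation, and no additional participants.

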### Recruitment and Enrollment

CBO clusters are members of TBR selected to account for geographic and socioeconomic diversity. Clusters are enrolled by program staff who work with the CBO leadership to identify qualified CFs and enroll eligible participants. Engagement efforts emphasize building relationships with trusted local leaders and inclusive outreach that uses culturally relevant materials and ensures transparency. CFs deliver the intervention and recruit participants. Licensed mental health professionals (eg, licensed master or clinical social worker, licensed professional counselor, or licensed marriage and family therapist) or individuals with experience in group or community facilitation, who are affiliated with a TBR institution, and who are willing to commit to the training and delivery of all components of the intervention are eligible to be a CF. To every extent possible, CFs are members or strongly affiliated with the cluster where they are delivering the COPE intervention. In some cases, however, trained CFs may facilitate for a cluster with which they are not strongly affiliated.

Potentially eligible participants will be recruited by the CFs and leaders at each participating cluster CBO. This will be accomplished by a combination of posting fliers, announcements at critical meetings, word of mouth, phone, and social media, as appropriate to each cluster. Enrolled participants will be those who signed the informed consent and completed the baseline (T1) assessment.

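### Participants are recruited after their cluster's arm has been drawn and left unconcealed, so who enrols can depend on the arm

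*Protocol article*

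**What the plan says.** The order of events is set out in three sections of the protocol article.

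- Overview and Study Design: "At the initiation of a step and before participant enrollment, clusters are randomized into study arms". The same section says "Allocation into intervention or control arms will not be concealed at either the cluster or individual level", and continues "nor will clusters or participants be blinded, as doing so is not feasible given the group-based nature of the intervention", adding the community-based implementation as a further ground. T1 comes after the draw: "Presurvey data collection will occur immediately before the start of the intervention within each cluster".
- Sampling Strategies and Sample Size: "After clusters are randomized into groups, participants will be recruited by CFs and project staff using convenience sampling techniques".
- Recruitment and Enrollment: "CFs deliver the intervention and recruit participants"; "Potentially eligible participants will be recruited by the CFs and leaders at each participating cluster CBO"; and "Enrolled participants will be those who signed the informed consent and completed the baseline (T1) assessment".

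Two mitigations are stated: unspecified controls for differences in timing and enrolment (Overview and Study Design), and model covariates such as age, ethnicity and education (Aim 2: Testing of Intervention Effects). Potential Limitations covers clustering, calendar time and attrition, but not differential recruitment.

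**The concern.** Randomising clusters protects the comparison of clusters. It protects the comparison of participants only if the arm has no influence on who is approached and who accepts. Here the cohort is formed by consent plus T1, both after an unconcealed draw. The sample is a convenience sample, and some of the recruiters will also deliver the sessions. If more distressed or more motivated people join one arm, the arms differ at T1 for reasons unrelated to COPE. Intention-to-treat analysis cannot repair this, because people who stayed away because of the arm never enter the analysis set. The primary outcomes are unblinded self-reports of distress, which are directly exposed to such differences.

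The exposure is also partly avoidable. A group intervention cannot be hidden from those attending it, but an arm can be withheld until a sign-up list is closed.

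**Working it through.** **Sequence.** Read together, the sections give: arm drawn, not concealed; then recruitment; then consent and T1; then content. Nothing places sign-up or consent before the draw.

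**Route for selection.** Willingness to take part in the intervention is an inclusion criterion in both arms, and every cluster receives COPE. What differs is the first meeting (4 hours of COPE, or about 1.5 hours of house meeting) and when COPE starts (first or third meeting).

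**Size.** The plan has no figure to reproduce, so this is a what-if calculation.

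Inputs from Sampling Strategies and Sample Size: ICC 0.10, within-person correlation 0.3, 20 participants per cluster, target effect 0.3 SD.

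Assumed: an imbalance of 0.2 SD; cluster autocorrelation k from 1.0 to 0.6; within-person correlation applied to the person-level variance of 0.90 (0.27 stable, 0.63 residual); T1 coded as unexposed in both arms; complete data; categorical time; no random slopes.

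For cluster means, the covariance between two time points is `a = 0.10k + 0.27/20`, and the extra variance at each time point is `b = 0.10(1-k) + 0.63/20`.

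- k = 1.0: a = 0.1135, b = 0.0315, b + 3a = 0.372
- k = 0.6: a = 0.0735, b = 0.0715, b + 3a = 0.292

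The arms differ in exposure only at T2 and T3. The generalised least squares estimate is therefore the mean arm difference at T2 and T3, minus w times the mean arm difference at T1, T4 and T5, with `w = 3a/(b+3a)`. This does not depend on the number of clusters or their split.

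1. *Stable imbalance of 0.2 SD at all time points.* Shift = `0.2 × b/(b+3a)`. For k = 1.0: 0.2 × 0.0315/0.372 = 0.017. For k = 0.6: 0.2 × 0.0715/0.292 = 0.049. That is 6% to 16% of 0.3. A plain comparison at T2 or T3 shifts by 0.2, or 67% of 0.3.

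2. *Imbalance of 0.2 SD at T1, falling to 0.2r afterwards (r = 0.3 to 0.7).* Shift = `0.2 × [r(a+b) - a]/(b+3a)`. The extremes are 0.2 × (0.0435 - 0.1135)/0.372 = -0.038 and 0.2 × (0.1015 - 0.0735)/0.292 = +0.019. A change-from-baseline contrast moves by 0.2(1 - r), which is 0.06 to 0.14 SD in size, or 20% to 47% of 0.3.

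3. *Readiness to change: no difference at T1, a difference g from T2 onwards.* Shift = `g × (a+b)/(b+3a)`, which is 0.145/0.372 = 39% to 0.145/0.292 = 50% of g. A T2 or T3 contrast carries all of g, with or without adjustment for T1.

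**Could the T1 table rule it out?** With 15 clusters split 8 and 7 (the split is assumed), the standard error of the T1 arm difference is sqrt[(0.10 + 0.90/20) × (1/8 + 1/7)] = 0.197. An imbalance of 0.2 SD is about one standard error and could pass as chance.

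**The case against.** The strongest reply is that the design narrows the problem and the model absorbs most of what is left. That largely stands for the primary analysis. T1 precedes content, every cluster crosses over, and the calculation above shows how little of a stable imbalance survives. The trial also follows reporting guidance for stepped-wedge trials and has a flow diagram (not shown), which may already give some of the counts.

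Several stronger readings are tempting, and the document does not support them.

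- A reader might infer that invitees choose between COPE and a listening session. They do not: both arms join a programme containing COPE.
- A reader might set 0.2 SD against the 0.3 target and infer that two thirds of the planned effect is at risk in the primary result. That holds only for a plain T2 or T3 comparison, and the 0.2 is an assumption.
- A reader might infer that fliers announce the arm, or that whoever draws the allocation also recruits. Neither is stated. That recruits know the arm is an inference from the lack of concealment, though a reasonable one given the different first meetings.
- A reader might say the infeasibility claim is simply false. The sentence gives two grounds and may be meant for blinding alone. Ethical Considerations also commits the team to communicating timelines clearly. None of this prevents announcing the arm after sign-up. If the grounds cover blinding only, no reason is given for leaving allocation unconcealed.

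The stated controls for enrolment differences are too unspecific to judge, and demographic covariates do not measure motivation or distress.

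**Conclusion.** The point holds as a design weakness of moderate size. The sequence is explicit: draw, no concealment, recruitment, enrolment. Under the assumed stable 0.2 SD imbalance, the five-time-point estimate moves by about 0.02 to 0.05 SD; if the imbalance partly regresses, by -0.04 to +0.02 SD. The exposure is greater for between-arm contrasts at T2 and T3, the only time points at which one arm has had COPE and the other has not. Aim 2 uses the period before the switch in a sensitivity analysis for this reason. Such a contrast carries the full 0.2 SD if unadjusted. Differences in readiness to change are not removed by a cluster intercept or by T1 adjustment.

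These figures rest on the listed assumptions and on a simplified form of the planned model. The direction and actual size of any bias cannot be derived from the document.

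**What to change.** **Clusters not yet recruited.** Close the sign-up list and take consent before that step's arm is drawn or announced. Leave T1 where it is; moving it earlier would add a contact and alter the assessment intervals. The cost is that invitees commit without knowing the format of the first meeting, and some may drop out before T1. That loss can at least be counted by arm. Recruitment was due to end in spring 2025 and the article is dated 20 May 2025, so few or no clusters may remain.

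**Clusters already run.**
- Report by arm the numbers signed up, consented and T1-complete, with T1 scores. Do not read a non-significant T1 difference as evidence of balance.
- Make any T1 to T3 between-arm contrast account for the participant's own T1 score. The article names no such covariate, so it has to be specified.
- Name differential recruitment after an unconcealed draw in Potential Limitations.

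In Overview and Study Design, give the reason for not concealing allocation separately from the reason for not blinding. These steps need only records and analysis text, although sign-up numbers may not have been kept for the early steps; if so, say so.
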